### Interim analyses {21b}

No interim analysis is planned.

### Methods for additional analyses (e.g., subgroup analyses) {20b}

Further sensitivity analyses for the primary endpoint include the performance of a Satterthwaite test (Welch test) for the comparison of the FAS score between the three treatment arms in the case of unequal variances in the respective groups, and in case of falsely documented stratification factors (if revealed after randomization), the repetition of the primary analysis with the correct values. Subgroup analyses will be performed at least for the stratification factors of the randomization sex (male/female) and BMI (< 30/≥ 30 kg/m^2^).

Adverse (AE) and serious adverse events (SAE) are documented and descriptively evaluated. AEs and SAEs are compared between the therapy groups using a chi-square test.

### Methods in analysis to handle protocol non-adherence and any statistical methods to handle missing data {20c}

The primary analysis will be performed in the ITT population, which is in line with the treatment policy strategy to handle intercurrent events, i.e., patients will be analyzed as randomized regardless of the experience of an intercurrent event. Missing values will be replaced using a conservative LOCF approach. A per-protocol (PP) and a complete-case (CC) analysis will be conducted in line with the primary analysis as sensitivity analyses. Patients who (a) do not prematurely ended the trial (i.e., no withdrawal of informed consent, intolerable adverse events, occurrence of an exclusion criterion, premature therapy end by the patient, and other circumstances that would compromise a patient’s health in case of further trial participation) and (b) have a FAS score at 3 months (end of intervention, visit 2) are included in the PP population. The CC population comprises patients who are (a) included in the PP population, (b) participated in at least 5 out of 6 sessions á 50 min or 10 out of 12 sessions á 25 min, (c) have a FAS score at 3 months (end of intervention, visit 2), and (d) do not show any other compliance violations (e.g., not using the wearables, large time period between planned and performed visit (</> 10 days)).

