### Intervention description {11a}

The study consists of three arms, each including 300 min of online therapy sessions over a period of 3 months, and a follow-up period of 3 months (6 months after BSL). The therapy consists of 300-min online intervention with 50-min sessions every 2 weeks (alternatively up to 12 × 25 min every week). The interventions are led by an exercise scientist and a psychological psychotherapist, respectively.

In the exercise therapy intervention, an individual exercise plan will be developed during the first online session based on the results of the aptitude test and the participant’s descriptions and routines. This exercise plan includes managing daily activities, a heart rate limit, moderate endurance and strength exercises, as well as stretching and relaxation exercises. To account for the physical inactivity caused by fatigue in many participants, light strengthening exercises (e.g., chair squats and wall push-ups) and shorter endurance exercises (e.g., walking, ergometer training, Nordic walking, cycling) will be usually performed at the beginning. If participants are currently receiving therapy, such as regular physiotherapy or ergotherapy, this will be integrated into the exercise plan and planned around it. The exercise plan aims to increase the frequency of strength and endurance training stimuli and to adjust the intensity to individual circumstances without causing overload or crashes. The activities are recorded using a wearable device. To ensure subjectivity of the intensities, the patients will keep a training diary during the intervention, in which the subjective feeling of exertion is assessed using the Borg scale and the daily feeling in the morning and in the evening (scale 1–10) is documented. During therapy sessions, activities will be discussed and exercise plans and the time between sessions will be considered. This includes wearable data, training diaries, sleep patterns, recovery, and existing therapies such as physiotherapy and occupational therapy. Other strenuous activities, such as cognitive activities, will also be taken into consideration as well as the physiology of training, fatigue, and recovery. The exercise therapy aims to improve reduced resilience and fatigue without overwhelming patients with volume or intensity. This will be achieved through a comprehensive approach that allows patients to engage in continuous, daily physical activity.

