In the psychotherapeutic intervention, a modularized, coping-oriented short-term therapy based on the individual needs of the patient will be performed taking into account the specific deficits identified in the psychosomatic evaluation at baseline. The sessions focus on the following topics: (1) psychoeducation, (2) mindfulness regarding one’s own stress limits, (3) time and energy management based on self-observation to prevent crashes, (4) improving self-care and resources, (5) differentiate between helpful and less helpful coping strategies, and (6) consideration and treatment of mental comorbidity.

Within the sessions, starting points will be identified with the patients, which the patients can work on independently between sessions.

In the combined intervention, 12 sessions à 25 min will be performed alternating between psychotherapy and exercise therapy. The contents of the interventions are the same as described; however, due to the same amount of therapy in all three study groups, the treatment content in the combined study group is conveyed in a condensed form.

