### Criteria for discontinuing or modifying allocated interventions {11b}

One or more of the following circumstances may lead to premature termination of the study for an individual subject: withdrawal of the subject’s consent, occurrence of an exclusion criterion, therapy discontinuation by the patient (not attending therapy visits or documenting discussed therapy contents), and other circumstances that would to lead to worsening of PCS symptoms if continuing the study. For the benefit and interest of the participant, the investigator can terminate study participation at any time if serious side effects or other unforeseeable circumstances occur that endanger the health of the participant. In this case, the Ethics Committee of Hannover Medical School will be informed.

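### The complete-case set excludes patients for not using a wearable that the psychotherapy arm is not described as having, so this sensitivity analysis is filtered on one side for combination versus psychotherapy

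*Protocol article*

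**What the plan says.** Section {20c} makes the intention-to-treat analysis primary and adds two restricted sets: "A per-protocol (PP) and a complete-case (CC) analysis will be conducted in line with the primary analysis as sensitivity analyses". The per-protocol (PP) set requires that the patient did not leave the trial early and has a 3-month FAS score. The CC set is nested in the PP set and adds attendance (five of six 50-minute sessions or ten of twelve 25-minute sessions) and a final item (d), that patients "do not show any other compliance violations (e.g., not using the wearables, large time period between planned and performed visit", with a limit of 10 days. Item (d) is not restricted to any arm.

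The wearable appears in section {11a} within the exercise-therapy description: "The activities are recorded using a wearable device". The training diary stands beside it: "the patients will keep a training diary during the intervention". The Abstract likewise lists day-to-day activity tracking under exercise therapy. The psychotherapy description names no device. Its work between sessions is put this way: "starting points will be identified with the patients, which the patients can work on independently between sessions". The combination arm receives the content of both therapies in condensed form.

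The Confidentiality section {27} names the tracker and its data route without saying which arms use it. Table 1, the schedule, is not shown in the text available.

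**The concern.** Wearable use is observed after randomisation. Excluding on it is tolerable in a sensitivity analysis if both arms of a comparison face the same test. Here the test appears to exist in only one arm of combination versus psychotherapy. A combination patient who attends every session, completes the 3-month FAS on time and leaves the watch in a drawer is excluded. A psychotherapy patient with the same record has no watch to neglect and stays in.

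If stopping the device goes with a poorer course, which is plausible in a fatigue trial but nowhere stated, the retained combination group is the better part of that arm and is compared with a psychotherapy group not selected in this way. The CC result would then tend to confirm a positive primary result instead of testing it. Combination versus exercise is less exposed, because both of those arms have the device.

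**Working it through.** **Which comparison is affected.** Set side by side, the texts give:

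- Exercise: wearable described ({11a}), so item (d) can exclude.
- Combination: exercise content inherited ({11a}), so item (d) can exclude.
- Psychotherapy: no wearable described ({11a}), so the wearable part of item (d) cannot exclude.

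The one-sided contrast is therefore combination versus psychotherapy.

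**The plan's own figures (section {14}).** Difference 2.5, SD 5.0, two-sided 5%, power 80%. The normal approximation is n = 2 × (1.96 + 0.842)² × (5.0/2.5)² = 62.8, so 63 per group. With the noncentral t, power is 79.5% at 63 and 80.1% at 64, so the stated 64 is reproduced. The Satterthwaite case (SDs 5.8 and 5.0, difference 7.2 − 4.5 = 2.7, n = 64) gives 79.9%, as stated. Exercise versus combination (difference 5.0) gives more than 99%, as stated. None of these figures is in dispute. They show that combination versus psychotherapy is the tighter of the two co-primary comparisons.

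**Size of a one-sided filter.** The documents give neither a rate of wearable non-use nor its relation to outcome, so both are assumptions. Let q be the share of combination patients excluded and d the amount by which they improve less than the rest. If the retained patients improve by m on average, the whole arm improves by (1 − q)m + q(m − d) = m − qd. Excluding the non-wearers raises the arm mean by q × d.

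- d = 0: shift 0 for any q.
- q = 10%, d = 2: 0.2 points, 0.2/2.5 = 8% of the planned difference.
- q = 20%, d = 4: 0.8 points, 0.8/2.5 = 32%.

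**Chance of a nominally significant CC result favouring the combination when the full arms do not differ.** Normal approximation, SDs 5.0 (combination) and 5.8 (psychotherapy), n = 65(1 − q) against 65, no other exclusions: 1 − Φ(1.96 − qd/SE), with SE = √(25/[65(1 − q)] + 33.64/65). Without the filter it is 2.5%.

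- q = 10%, d = 3: shift 0.3, SE 0.972, 1 − Φ(1.651) = 4.9%.
- q = 20%, d = 3: shift 0.6, SE 0.999, 1 − Φ(1.360) = 8.7%.
- q = 20%, d = 4: shift 0.8, SE 0.999, 1 − Φ(1.159) = 12.3%.

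**Cross-check with a different model.** Let adherence be a latent normal variable correlated r with improvement, and drop the lowest share w from the combination arm only. Bias = SD × r × φ(z_w)/(1 − w), with SD 5.0. For w = 10%, r = 0.2 this gives 0.19 points; for w = 20%, r = 0.3, 0.52; for w = 30%, r = 0.5, 1.24; and 0 whenever r = 0. Over w = 5-30% and r = 0-0.5 the bias runs from 0 to about 1.2 points. Both models start at zero and give several tenths of a point for moderate assumptions.

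**The case against.** The strongest reply is that the text available may not settle who wears the device. Section {27} does not limit the tracker to an arm, Table 1 is not shown, and a journal article condenses the full protocol. That stands as a condition on the point. It does not remove it: {27} introduces its applications as support for delivering the intervention and does not say that all arms wear the tracker, while the Abstract and {11a} place tracking under exercise therapy. A reader might go further and call all-arm wear a contradiction of {11a}. Silence about a device is not a contradiction; in that case the sections would only need to be reconciled.

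It can also be said that the impact is small. Trial success rests on the intention-to-treat ANCOVA, the CC analysis carries no alpha, and a PP analysis without a wearable criterion is already planned. This stands and limits the weight of the point. The magnitude is also assumed, including its direction, since nothing in the documents says that non-wearers improve less.

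Three stronger readings are tempting and not supported:

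- *Missing therapy documentation filters the PP set on one side.* Section {11b} counts as a possible ground for ending participation "therapy discontinuation by the patient (not attending therapy visits or documenting discussed therapy contents". That wording covers any arm, and the section says only that such circumstances may lead to termination. The PP definition speaks of "premature therapy end by the patient, and other circumstances that would compromise" a patient's health, and repeats no documentation rule. The psychotherapy topics include "time and energy management based on self-observation to prevent crashes", so record-keeping in that arm is not excluded. Only the training diary is specific to exercise.
- *Non-compliant psychotherapy patients cannot be excluded at all.* Item (d) is an open list and includes the visit window, and both can reach them.
- *The trial's type I error is inflated.* The percentages in the working describe a supportive analysis.

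Finally, adherence to home exercise is naturally specific to the arms that have it. That is true, but wearing a watch is a measurement step and not receipt of therapy, so little is lost by leaving it out.

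**Conclusion.** The point holds for the CC set and for combination versus psychotherapy, on the intervention descriptions as written. The wearable criterion is a post-randomisation exclusion that only one of those two arms can fail, and it may favour the combination if non-wearers improve less. The size cannot be determined from the documents: 0 if non-use is unrelated to outcome, and about 0.2 to 0.8 FAS points if 10-20% of combination patients are excluded and improve 2-4 points less. The calculation further assumes no other exclusions and unchanged SDs. The consequence is confined to the value of the CC analysis as a robustness check. The primary analysis and the sample size are untouched, and no one-sided effect on the PP set can be read from the text. It is worth correcting before the data are analysed, and does not threaten the trial's main conclusion.

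**What to change.** In {20c}, define CC compliance by the criteria there that apply to every arm: attendance (five of six or ten of twelve sessions), a 3-month FAS score and the 10-day visit window. Remove wearable non-use from item (d), and report wearable use descriptively in the arms that have the device. If the criterion is kept, also report the CC comparison of combination with psychotherapy without it, so that the effect of the filter can be seen.

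State which arms use the tracker. If all three do, bring the intervention descriptions in {11a} into line with {20c}.

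The cost is about one sentence in the set definitions. The downside is that the CC set no longer reflects monitoring of home exercise; the descriptive report of wearable use covers part of that loss.

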### Plans to give access to the full protocol, participant-level data and statistical code {31c}

The study data (as SPSS or SAS data set) and the statistical code will be provided upon request by the Institute for Biostatistics at the study end and after finalization of the clinical study report. Before data bank closure, no data will be disclosed.

## Oversight and monitoring

### Composition of the coordinating center and trial steering committee {5d}

The Department of Rehabilitation and Sports Medicine acts as the coordinating center. The coordinating investigator and the principal investigator together with an expert psychiatrist, composing the trial steering committee, have bi-weekly meetings to discuss the study progress. The coordinating investigator is responsible for the day-to-day communication with the local principal investigators from the participating centers. Twice a year, members of the study group updating the funder of the study (COFONI network) on the study’s progress during scheduled meetings.

### Composition of the data monitoring committee, its role and reporting structure {21a}

There is no data monitoring committee for this trial, but as part of data monitoring the data management team at the Institute for Biostatistics will check the collected and documented data in the SoSci-Survey Tool and the eCRF for completeness and plausibility.

### Adverse event reporting and harms {22}

Adverse and serious adverse events have been predefined by the study team. They are both documented in the study registry (ClinicalTrials.gov Identifier: NCT06042751). Serious adverse events and other unintended effects are discussed in the investigator team and reported to the responsible ethic committee.

### Frequency and plans for auditing trial conduct {23}

The data management team will provide a monitoring report every month for the general status and missing data. In addition, once a month the randomization status will be send to study PIs and study coordinators.

### Plans for communicating important protocol amendments to relevant parties (e.g., trial participants, ethical committees) {25}

During the trial, all protocol amendments and revised informed consent form are sent to the central EC for their review. Amendments are not implemented without prior review and documented approval/favorable opinion from the EC. After approval, important protocol modifications are directly communicated to the relevant parties and included in all necessary study documents.

### Dissemination plans {31a}

It is planned to publish the results of the study in a scientific journal under open access conditions and to present them to the specialist public at scientific congresses. In addition, a summary of the results in layman’s terms is planned for the participants and other interested citizens. It is planned to make the study manual available to other interested practitioners.

## Discussion

Even though the exact number of people affected is unknown, it can be assumed that a relevant number of patients is affected by PCS. The pathomechanisms behind the development of PCS are not yet sufficiently well understood, so that no causal therapies are available. Information on treatment trials trying to improve symptoms and dealing with the disease and the associated functional impairment are also limited [10]. Both, psychotherapeutic and exercise therapy concepts have been suggested as beneficial interventions for PCS, yet results are still inconsistent and not conclusive. A combination of both therapy approaches might have a synergistic effect on fatigue compared to unimodal therapies, a research question not addressed so far. Therefore, we planned an interventional trial based on previous literature-based and own experiences from the treatment of patients with PCS [8, 25] to compare the combination therapy to psychotherapeutic and exercise therapy concepts alone.

The importance of telemedical treatment services has grown considerably in recent years. This method is also planned for the current study, as it is believed to be particularly suited to severely impaired patients with limited energy and severe fatigue [26]. However, there is still a paucity of data globally and from Germany on the acceptance and feasibility of such treatment programs for PCS patients [27]. It is essential to elucidate the extent to which these forms of medical intervention are accepted by the participants in our study, as this will inform about the feasibility and transferability of these treatment options into routine clinical practice. Possible problems in the course of the study will include whether patients will be sufficiently recruited and whether acceptance and willingness to participate in our study will be sufficiently high. In this context, the course and prevalence of PCS to date and in the near future is hardly to project which might affect the recruitment process and duration of the study.

## Trial status

Protocol version: 3.1, protocol date: 6 December 2023. Date of start recruitment: December 12, 2023. Approximate date of recruitment completion: March 2025.

## Data Availability

Data will be uploaded to the data repository of the funder (COFONI network) and will be publicly available.

## Abbreviations

AE: Adverse event
BMI: Body mass index
CC: Complete-case
CFS: Chalder Fatigue Scale
eCRF: Electronic case report form
GCP: Good clinical practice
FAS: Fatigue Assessment Scale
HADS-D: Hospital Anxiety and Depression Scale
IPQ: Brief Illness Perception Questionnaire
ITT: Intention-to-treat
LOCF: Last-observation-carried-forward
MFI-20: Multidimensional Fatigue Inventory questionnaire
MHH: Hannover Medical School
PCR: Real-time quantitative reverse transcriptase polymerase chain reaction
PCS: Post-COVID-19 syndrome
PEM: Post-exertional malaise
PP: Per-protocol
RCT: Randomized controlled trials
SAE: Serious adverse events
SD: Standard deviation
SF-36: Short Form-36 Health Survey
WAI: Work Ability Index
WHO: World Health Organization
